**Table 1 Tab1:** **Stepping criteria**

Pre-treatment score	Score at end of GSH	Criteria	Action	Decision
Any	0-9	Patient is unambiguously below diagnostic cut-off	Inform participant that treatment is ended as a consequence of them no longer meeting diagnostic criteria	Discharge
19-27	10-12	Patient is within suggested diagnostic cut-off range and has made around 50% improvement	Discuss with participant and suggest discharge due to good rate of progress	Step up or discharge depending on participant’s wishes
<19	10-12	Patient is within suggested diagnostic cut-off range and has made less than 50% improvement	Discuss with participant and suggest stepping up to increase progress further	Step up or discharge depending on participant’s wishes
Any	13-27	Patient is unambiguously above diagnostic cut-off	Offer CBT to participant	Step up

Criteria to determine if stepped care patients are discharged from treatment following guided self-help (GSH) or ‘step up’ to cognitive behaviour therapy (CBT).

High-intensity psychological therapy will be CBT delivered by therapists following a treatment protocol based on the standard manuals published by Beck and colleagues
[38] and used in two of our other recent trials
[30, 32]. Early sessions will focus on agreeing problems to be addressed, therapeutic goals and learning about the CBT model and techniques for behaviour change. Patients will subsequently work on negative automatic thoughts, maladaptive beliefs and, where indicated, underlying core beliefs. Later sessions will help patients anticipate and practice managing their response to stressors which could lead to future relapse. Specific CBT techniques that may be used will include scheduling activity and mastery behaviours and the use of thought records. All sessions will be face-to-face and consistent with National Institute for Health and Care Excellence recommendations for duration and frequency (that is, between 8 and 20, 50-minute consultations over a maximum of 16 weeks
[10]).

#### Intensive psychological therapy alone

High-intensity psychological therapy for participants in the control arm of the trial will be identical to the high-intensity treatment for patients in stepped care except that patients will only have intensive CBT; they will not be offered GSH first.

#### Outcomes

Given this is a feasibility study with a range of different aims to inform a fully powered evaluation of stepped care, there is no single primary outcome measure. Rather a variety of patient-related data will be collected at baseline and 8 months’ post-randomisation: severity of depressive symptoms (BDI-I)
[27], health-related quality of life (Short Form Health Survey-36; SF-36)
[39] and worry and anxiety (Generalised Anxiety Disorder-7; GAD-7)
[40]. At 6 months’ post-randomisation we anticipate that treatment for patients, including those who are randomised to stepped care and step up to CBT, will be complete. We will also collect data on the flow of participants through the trial (that is, numbers of participants at each step) and the number and proportion of people who step up and are discharged from stepped care following low-intensity psychological therapy. Therapists will collect data on treatment adherence and content; they will log all patient contacts and record key themes covered at each treatment session using an agreed, semi-structured form.

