**Methods/Design:**

STEPS (Developing stepped care treatment for depression) is a mixed methods study to address uncertainties associated with a large-scale evaluation of stepped care compared with high-intensity psychological therapy alone for the treatment of depression. We will conduct a pilot randomised controlled trial with an embedded process study. Quantitative trial data on recruitment, retention and the pathway of patients through treatment will be used to assess feasibility. Outcome data on the effects of stepped care compared with high-intensity therapy alone will inform a sample size calculation for a definitive trial. Qualitative interviews will be undertaken to explore what people think of our trial methods and procedures and the stepped care intervention. A minimum of 60 patients with Major Depressive Disorder will be recruited from an Improving Access to Psychological Therapies service and randomly allocated to receive stepped care or intensive psychological therapy alone. All treatments will be delivered at clinic facilities within the University of Exeter. Quantitative patient-related data on depressive symptoms, worry and anxiety and quality of life will be collected at baseline and 6 months. The pilot trial and interviews will be undertaken concurrently. Quantitative and qualitative data will be analysed separately and then integrated.

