#### Sample size

A conventional power calculation is inappropriate for the purpose of a pilot RCT
[23, 41]. Instead, we have calculated the sample size required based on the margins of error associated with the key parameters of interest, specifically: recruitment and follow-up rates; the standard deviation of the primary outcome (and other continuous outcomes); and the correlation between baseline and 6 month follow-up outcome scores, which can be used to refine the sample size calculation for the fully powered evaluation to take into account the added precision gained from adjusting for baseline scores when comparing the follow-up outcome scores between the trial arms.

We expect to approach a total of 1,500 patients to participate in the feasibility trial. This is large enough to estimate a participation rate (as percentage of subjects approached) of 5% with a margin of error of ±1.1% or to estimate a participation rate of 10% with a margin of error of ±1.5% based on 95% confidence intervals. However, if we need to approach a higher number of potential participants (2,000) and achieve a lower participation rate of 2%, the associated margin of error will be ±0.7% based on 95% confidence intervals.

If we assume the participation rate will be 5% of 1,500 people approached, then the feasibility trial would recruit 75 participants. This is sufficient to: (i) estimate a follow-up rate (as percentage of participants recruited) of 80% with a margin of error of ±9%; (ii) estimate the standard deviation of the continuous primary outcome to within 22% of its true value based on the upper limit of the 95% confidence interval; (iii) estimate the correlation between the baseline and follow-up outcome scores with a margin of error of 0.12 (based on the lower limit of the 95% confidence interval) if the true correlation is 0.8. If we assume the participation rate will be 2% of 2,000 people approached, this is sufficient to: (i) estimate a follow-up rate of 80% with a margin of error of ±10.1%; and (ii) estimate the correlation between the baseline and follow-up outcome scores with a margin of error no greater than 0.13 (based on the lower limit of the 95% confidence interval).

We consider the margins of error associated with the recruitment of 75/1,500 people and 60/2,000 approached to be acceptable and have, therefore, selected a range of between 60 and 75 as our target sample size.

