#### Quantitative analysis

To address our first research question, "what is the quantifiable performance of recruitment and retention methods which may be used in a fully powered trial?", we will use count data to enumerate the flow of the participants through the trial. We will express count data both as a percentage of the total number of participants approached and in relation to the preceding step in recruitment. We will estimate margins of error for these parameters. For each of the interventions, we will quantify the number of participants who withdrew, could not be contacted or did not provide 6 month follow-up data for another reason. We will express numbers as a percentage of the total number of participants in each of the stepped care or high-intensity group. We will follow Consolidated Standards of Reporting Trials (CONSORT) guidelines

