[43] on reporting the number of participants who exit the trial at each step of recruitment and from whom we are unable to collect follow-up data. We will quantify the number and proportion of people who receive stepped care and step up from low- to high-intensity treatment or are discharged following low-intensity therapy (Question 2). To measure the variability in patient-related outcomes following stepped care or intensive psychological therapy and their correlation with patients’ baseline scores (Question 3) we will estimate the standard deviation around mean BDI-I, GAD-7 and SF-36 scores at baseline and 6 months for both groups. We will then estimate the correlation between participants’ scores on the BDI-I, GAD-7 and SF-36 at baseline and at 6 months. Quantitative data on the acceptability of stepped care (Question 5) will be analysed as follows. For each of the interventions we will generate descriptive statistics to describe the number of sessions attended. We will quantify the number and proportion of participants who declined any treatment, dropped out early or completed treatment. For stepped care participants, we will quantify the number and proportion who drop out prior to low-intensity therapy, before high-intensity therapy having been stepped up, and during each treatment step. Therapists’ thematic description of the content of high-intensity CBT that is received by patients in each of the intervention groups will be quantified and compared. We will analyse session content data to assess the extent to which GSH material and CBT are delivered in line with our clinical protocol for CBT and guidance on GSH.

All analyses will be on an intention to treat basis (that is, we will analyse participants in their original assigned groups). Emphasis will be on quantification and estimation rather than hypothesis testing. We will not impute missing data although we will report outcome data that are missing in both intervention groups and, to the extent that we are able, reasons for missing outcomes. We will conduct all analyses using STATA v.11 (STATA, StataCorp LP, College Station, TX, USA).

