### Forecast execution dates

The preparatory period started in April 2013. Recruitment is running from September 2013 for approximately 1 year. Follow-up and qualitative data will be collected from April 2014 to March 2015. Data analysis and reporting are forecast to take another 6 months. The total duration of the study will be 24 months.

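### Outcome follow-up is set at 8 months after randomisation in the Outcomes section and at 6 months everywhere else

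*Protocol article*

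**What the plan says.** The Outcomes section defines what is collected and when. It states that the patient-related measures "will be collected at baseline and 8 months" after randomisation, and names the BDI-I, SF-36 and GAD-7. Its next sentence gives 6 months as the point by which treatment is expected to be complete, including for stepped care patients who step up.

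Every other statement of the outcome follow-up time gives 6 months:

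- **Abstract, Methods/Design**, for the same three domains: "quality of life will be collected at baseline and 6 months".
- **Sample size**, among the parameters that the pilot is sized to estimate: "the correlation between baseline and 6 month follow-up outcome scores".
- **Quantitative analysis**, in the count of patients lost to follow-up: "did not provide 6 month follow-up data for another reason".
- **Quantitative analysis**, for the standard deviations: "SF-36 scores at baseline and 6 months for both groups".
- **Quantitative analysis**, for the correlations of the same three instruments with baseline: again 6 months.

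Forecast execution dates has recruitment running for about a year from September 2013 and adds: "Follow-up and qualitative data will be collected from April 2014 to March 2015".

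**The concern.** A single follow-up assessment cannot take place at both times, and the article does not say that there are two. The section a researcher would use to schedule the assessment disagrees with the sections an analyst would use to analyse it.

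The pilot exists to supply design inputs for a fully powered trial. Three of them depend on the follow-up interval: the proportion of patients followed up, the standard deviation of the outcome scores, and their correlation with baseline. The Sample size section says that the correlation will be used to refine the definitive trial's sample size. If the interval is ambiguous, anyone designing that trial cannot tell whether the estimates describe 6 or 8 months. The first and third research questions (recruitment and retention; outcome variability and correlation) are both affected.

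**Working it through.** This is a textual contradiction, so no sample-size formula decides it. Three checks bear on it.

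**1. Do the stated margins of error depend on the month?** The half-width for a follow-up rate is 1.96 × √(p(1 − p)/n).

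- n = 75, p = 0.80: 1.96 × √(0.80 × 0.20/75) = 9.05% (stated ±9%).
- n = 60, p = 0.80: 1.96 × √(0.80 × 0.20/60) = 10.12% (stated ±10.1%).

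Both figures reproduce and neither contains the follow-up month. The contradiction leaves the stated precision untouched. What it leaves open is which quantity is being estimated.

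**2. Which time fits the forecast dates?** Recruitment of about one year from September 2013 ends in August or September 2014.

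| Follow-up at | First assessment due | Last assessment due | Stated window |
|---|---|---|---|
| 6 months | March 2014 | February or March 2015 | April 2014 to March 2015 |
| 8 months | May 2014 | April or May 2015 | April 2014 to March 2015 |

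At 6 months the last assessments fall inside the window, and the first falls one month before it opens. At 8 months the last assessments fall one to two months after it closes.

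If recruitment is even (an assumption) and March 2015 is a firm close (also an assumption), patients recruited in the last one to two months would be missed under 8 months. That is 1/12 = 8% to 2/12 = 17% of the sample. For the target of 60 to 75 patients it is between 60 × 1/12 = 5 and 75 × 2/12 = 12.5, so roughly 5 to 13 patients.

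**3. Does the treatment schedule separate the two times?** The longest stepped care course is about 6 weeks of guided self-help contacts plus at most 16 weeks of CBT. That is 22 weeks, and 22/4.345 = 5.1 months, before any waiting time. Treatment should thus be over by 6 months, as the Outcomes section expects. Either time falls after that point, so the schedule does not decide between them.

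**The case against.** The contradiction itself is not open to dispute: both times stand in the current text and no section reconciles them. The case on the other side concerns how much it matters and how firmly 6 months can be inferred.

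- **The calendar is weak evidence.** The dates are forecasts, recruitment lasts only approximately a year, and the window also covers the interviews, which come before follow-up. The section does not add up either: April 2013 to March 2015 is already 24 months, a further 6 months of analysis makes 30, and the stated total is 24. This stands. The dates support 6 months but do not prove it, and the 8–17% figure is only illustrative.
- **The treatment-completion sentence does not set the assessment time.** It is equally compatible with a deliberate assessment at 8 months. This also stands. The inference to 6 months rests on the five statements elsewhere.
- **The practical risk is limited.** There is one recruiting service, one treatment clinic and one study researcher, so different sites reading the article differently is not the danger. The pilot has no single primary outcome and no emphasis on hypothesis testing, and the sample-size and analysis sections agree with each other, so the 8 is probably a slip. That may be so, but the reader cannot confirm it. If 8 months is deliberate, the abstract, sample-size and analysis sections are wrong instead.

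**Conclusion.** The point holds. The article gives 8 months once and 6 months five times for the same outcome assessment, and one or the other must be wrong. It affects all three patient-reported instruments, the follow-up rate, and the first and third research questions. No stated margin of error changes.

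This is more than a clerical matter, because the interval determines what the pilot's main quantitative outputs mean, and data collected only at 8 months could not support the analyses as written. That 6 months is the intended time is likely from the weight of the text, with modest support from the forecast dates. The conclusion that the plan contradicts itself does not depend on that inference, nor on the assumptions behind the 8–17% figure.

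**What to change.** The sponsor should confirm the intended time and make the article agree with itself.

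- **If 6 months is intended:** change the follow-up time in the Outcomes section to 6 months after randomisation. This is a one-word correction.
- **If 8 months is intended:** change the abstract, the Sample size section and the retention, standard deviation and correlation statements in Quantitative analysis. Extend the data-collection window in Forecast execution dates to at least April or May 2015.
- **If both assessments are intended:** say so, and state which one supplies the follow-up rate, standard deviations and correlations for the definitive trial.

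The first option costs almost nothing. The second costs edits in several sections and a later close of data collection. The third adds an assessment for each patient. Recruitment was still under way when the article was written, so a prompt correction can still guide the remaining assessments.

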#### Sample size

A conventional power calculation is inappropriate for the purpose of a pilot RCT
[23, 41]. Instead, we have calculated the sample size required based on the margins of error associated with the key parameters of interest, specifically: recruitment and follow-up rates; the standard deviation of the primary outcome (and other continuous outcomes); and the correlation between baseline and 6 month follow-up outcome scores, which can be used to refine the sample size calculation for the fully powered evaluation to take into account the added precision gained from adjusting for baseline scores when comparing the follow-up outcome scores between the trial arms.

We expect to approach a total of 1,500 patients to participate in the feasibility trial. This is large enough to estimate a participation rate (as percentage of subjects approached) of 5% with a margin of error of ±1.1% or to estimate a participation rate of 10% with a margin of error of ±1.5% based on 95% confidence intervals. However, if we need to approach a higher number of potential participants (2,000) and achieve a lower participation rate of 2%, the associated margin of error will be ±0.7% based on 95% confidence intervals.

If we assume the participation rate will be 5% of 1,500 people approached, then the feasibility trial would recruit 75 participants. This is sufficient to: (i) estimate a follow-up rate (as percentage of participants recruited) of 80% with a margin of error of ±9%; (ii) estimate the standard deviation of the continuous primary outcome to within 22% of its true value based on the upper limit of the 95% confidence interval; (iii) estimate the correlation between the baseline and follow-up outcome scores with a margin of error of 0.12 (based on the lower limit of the 95% confidence interval) if the true correlation is 0.8. If we assume the participation rate will be 2% of 2,000 people approached, this is sufficient to: (i) estimate a follow-up rate of 80% with a margin of error of ±10.1%; and (ii) estimate the correlation between the baseline and follow-up outcome scores with a margin of error no greater than 0.13 (based on the lower limit of the 95% confidence interval).

We consider the margins of error associated with the recruitment of 75/1,500 people and 60/2,000 approached to be acceptable and have, therefore, selected a range of between 60 and 75 as our target sample size.

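### The 0.13 margin for the baseline/follow-up correlation is worded as an upper bound, but it is the value at one correlation (0.8) with 48 pairs

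*Protocol article*

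**What the plan says.** The Sample size section of the protocol article justifies the pilot's size by margins of error rather than power. One of the parameters is the correlation between baseline and follow-up scores, wanted for the definitive trial because of the "added precision gained from adjusting for baseline scores when comparing the follow-up outcome scores between the trial arms".

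Two scenarios are given.

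- **Larger:** 5% of 1,500 approached, and "then the feasibility trial would recruit 75 participants". The correlation is estimated "with a margin of error of 0.12 (based on the lower limit of the 95% confidence interval"), with the condition "if the true correlation is 0.8".
- **Smaller:** it opens "If we assume the participation rate will be 2% of 2,000 people approached, this is sufficient to" and claims to "estimate a follow-up rate of 80% with a margin of error of ±10.1"% and to estimate the correlation "with a margin of error no greater than 0.13 (based on the lower limit of the 95% confidence interval"). No correlation is named here.

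The section then calls the margins for "the recruitment of 75/1,500 people and 60/2,000 approached to be acceptable" and on that basis sets the target at 60 to 75. No correlation other than 0.8 appears in the article.

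**The concern.** For a fixed number of pairs, the distance from a positive correlation down to its lower 95% limit depends strongly on the correlation. It is small near 1 and widens as the correlation falls over most of the range. A figure calculated at 0.8 therefore cannot be a ceiling for lower values. The larger scenario states its condition; the smaller one drops it and adds wording that turns a point value into a bound.

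Two uses of the figure are at stake. It is among the margins called acceptable when the 60 to 75 target is set. It also tells the designers of the definitive trial how precisely this pilot will supply the correlation, through which adjustment for baseline scales the sample size by 1 − r². A reader who takes the sentence at its word would expect precision to within 0.13 whatever the correlation proves to be.

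**Working it through.** **Inputs (all from Sample size).** True correlation 0.8 (stated for the larger scenario only). Follow-up 80%. Recruits 75 and 60, giving 75 × 0.80 = 60 pairs and 60 × 0.80 = 48 pairs. Two-sided 95% interval, z = 1.96. Using the 80% rate to get the number of pairs is an inference. It is supported by the article's 22% margin for the standard deviation in the 75-participant scenario: the upper limit is 22.0% above with 60 observations, but 19.2% with 75.

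**Formula.** Fisher's z: margin = r − tanh(atanh(r) − 1.96/√(n − 3)).

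**Reproducing the stated figures.**

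- n = 48, r = 0.8: atanh(0.8) = 1.0986; 1.96/√45 = 0.2922; tanh(0.8064) = 0.668; margin 0.132. Stated: 0.13.
- n = 60, r = 0.8: 1.96/√57 = 0.2596; tanh(0.8390) = 0.685; margin 0.115. Stated: 0.12, so rounded up.

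Other sample sizes do not give 0.13 at r = 0.8: 75 pairs give 0.100, 40 give 0.149 and 32 give 0.174. The large-sample standard error (1 − r²)/√(n − 1) with 48 pairs gives 0.103.

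**Margin at other correlations.**

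| True r | 48 pairs | 60 pairs |
|---|---|---|
| 0.8 | 0.132 | 0.115 |
| 0.7 | 0.181 | 0.158 |
| 0.6 | 0.219 | 0.192 |
| 0.5 | 0.248 | 0.218 |
| 0.3 | 0.283 | 0.250 |
| Maximum | 0.290 (r about 0.145) | 0.258 (r about 0.13) |

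The 60-pair column serves both for 75 recruited with 80% followed up and for 60 recruited with none lost.

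**Where the bound stops holding.** With 48 pairs the margin passes 0.13 for r below about 0.804, and no longer rounds to 0.13 for r below about 0.795. With 60 pairs it passes 0.13 for r below about 0.77. At r = 0.5 with 48 pairs it is 0.248/0.13 = 1.9 times the stated figure; at the maximum it is 0.290/0.13 = 2.2 times.

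**The recruit count.** 2% × 2,000 = 40, not 60. The other margins point to 60:

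- Follow-up: 1.96 × √(0.8 × 0.2/60) = 10.1%, as stated; 40 recruits would give 12.4%.
- Participation: the article gives ±0.7% for 2,000 approached. A rate of 3% (60/2,000) gives 0.75%; 2% gives 0.61%.

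Taken literally, 40 recruits give a correlation margin at r = 0.8 of 0.149 if all are followed up, and 0.174 with 40 × 0.80 = 32 pairs. On the sentence's own premise, then, 0.13 fails even at 0.8.

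**The case against.** The strongest defence is that the condition was dropped, not that the sum was wrong. The preceding sentence names 0.8 for the same quantity, and the second list is an abbreviated parallel of the first. As the number reproduces at 0.8, the authors very probably carried the condition over. This explains where 0.13 comes from, and that part stands. But the text does not say it, and even on that reading the wording is true only for correlations of about 0.8 or more.

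It can also be said that the correlation is one parameter among several and that the Discussion ties the sample size to recruitment and retention. That limits the consequence. Still, the Sample size section lists the correlation among its key parameters and cites the margins as grounds for the target.

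A reader might go further in three ways, which the article does not support.

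- **That the definitive trial would be badly undersized.** Planning on 0.8 when the truth is 0.5 gives (1 − 0.64)/(1 − 0.25) = 0.36/0.75 = 48% of the patients needed. But nothing commits the later trial to 0.8. The Quantitative analysis section estimates the correlation from the pilot data, and that estimate and its own interval will supersede the planning value. If the truth were 0.5, an observed 0.8 with 48 pairs would lie (1.099 − 0.549) × √45 ≈ 3.7 standard errors away on the z scale.
- **That 0.8 is optimistic.** It is given without a reason, but the article contains no evidence on the likely value. Entry rests on an interview diagnosis, with no stated score threshold on the depression inventory.
- **That the definitive calculation must use the lower confidence limit.** That is a debatable choice for a different trial and need not be fixed here.

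**Conclusion.** The sentence is wrong as written. The 0.13 is a point value at a correlation of 0.8 with 48 pairs. A bound valid for every correlation would be about 0.29 with 48 pairs or 0.26 with 60. The recruit count in the same sentence also conflicts with the 60 used to reach the figure.

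This rests on Fisher's z and on 80% follow-up, which together reproduce the article's figures (0.12 only by rounding up). The correlations below 0.8 are assumed values that show the sensitivity; the article offers none, and nothing here says which is likely.

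The fault lies in a precision statement. It does not invalidate the pilot, show that 60 to 75 is too few, or establish harm to the definitive trial.

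**What to change.** In the Sample size section:

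1. Delete *no greater than* and state that 0.13 assumes a true correlation of 0.8 and 48 participants followed up (60 recruited, 80% retained).
2. Reconcile the participation premise with the recruit count: 60 of 2,000 is 3%, and 2% is 40. Restate the margins that depend on it.
3. Give the lower-limit margin over an assumed range of correlations, for example 0.3 to 0.8, for 48 and 60 pairs, as in the table above.
4. Judge whether the 60 to 75 target is acceptable, and describe the precision passed to the definitive calculation, on those figures.

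The cost is a few lines of text and a less favourable statement of precision. It requires no extra patients and no change to design or analysis.
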